## Abstract

**Background:**

Focus on interventions for orphans and vulnerable children (OVC) in South Africa on education, quality of life (QoL) and nutrition-related matters have been reported diminutive. The risk of dropping out of school for an OVC with poor QoL and without varied food intake is very high. The problem with poor; QoL, nutritional care and academic performance (AP) of the OVC is that it sets the foundation for their adults’ life. The purpose of this longitudinal study is to develop, implement and to test the efficacy of an evidence-based nutrition education programme (NEP) for OVC that will integrate their families/caregivers, schools and communities.

**Methods:**

A longitudinal study, and a mixed-methods approach steered by action research will be used. This study will be in three phases. Phase 1 will be the needs assessment; Phase 2 will be the development of nutritional education materials, and Phase 3 is the intervention. QoL, dietary intakes, body composition, and anthropometric status, physical activities, and AP of 520 OVC in Soweto will be assessed using standard techniques. Nutrition knowledge, attitude and practices (KAP) of the caregivers will be assessed using previously validated questionnaires. Focus group discussion (FGD) will be conducted to gain an in-depth understanding of what OVC eat and factors affecting their food intakes. Data will be collected at baseline, week 12 and week 24. Generalised Least Squares (GLS) regression model will be used to test the study hypotheses. Atlas-ti and Thematic Framework Analysis (TFA) will be used for qualitative data analysis.

**Discussion:**

This study will provide detailed information on the QoL, food intakes concerning academic performance and general well-being of OVC in an Africa setting. The participatory mixed methods nature of the study will provide valuable insights into the drivers and challenges to QoL, AP, and nutritional status of this group. This approach will assist the policymakers’ and other stakeholders in decision making regarding the general well-being of the OVC.

**Trial registration:**

ISRCTN12835783. Date registered 14.01.2019.

## Background

The World Health Organization in 2016 reported that 15,000 deaths occurred among children per day translating into 5.6 million annually [1, 2]. More than 50% of the deaths are preventable using appropriate and evidenced-based intervention [3, 4]. Numerous scientific reports have described malnutrition as the key underlying and sensitive risks factors of vulnerability to early grave among the children [2].

Global provision of appropriate health care for orphans and vulnerable (OVC) children is critical for maximising their health well-being, potential, and quality of life (QoL) [4, 5].

Although there is considerable progress between 1990 and 2017 in reducing child mortality rates from 5.1 million to 2.6 million, it is unfortunate that the rates of progress have been reported lower than the rates of the negative impacts that children’s mortality rates have on the economic growths of the 52 nations of the world.

Nutrition-related factors contributed to 45% of deaths among the children [2].

Various interventions have been proposed and implemented in different parts of the world for OVC [6, 7]. The need to improve the nature of varied food intake among OVC in Africa has well been documented [8]. Unfortunately, the use of an evidence-based nutrition education programme (ENEP) as a component of reducing malnutrition and child mortality has not been explored fully in most of the African countries such as South Africa.

There is evidence that nutritional knowledge of caregivers/families is positively associated with the nutritional status of the children under their custody [9]. This may be the reason why nutrition-related factors were reported to contribute to 45% of deaths among the children [2].

Therefore, exploration of the risk factors that may be responsible for children to be vulnerable may be appropriate in designing more effective nutrition education intervention against malnutrition. An in depth understanding of the factors that can prevent OVC from attaining their potentials in life, such as QoL, dietary intakes, physical activities and anthropometric status concerning academic performance will be useful in developing and implementing nutrition education programme (NEP) for OVC.

Several factors can result in a child being characterised as vulnerable such as parent’s financial constraints, consistent domestic conflicts, malnutrition, unwanted by parents or caregiver, orphaned by the death of either or both parents as a result of natural deaths or diseases such as HIV [10]. Part of the worst-case scenario that can make a child vulnerable is when a child contact disease such as HIV after birth while the parents are HIV-negative. South Africa has 3.7 million orphans, and more than 50% of them were made orphans as a result of HIV/AIDS [1]. According to UNICEF reports, as at the end of 2016, South Africa has the second highest number of orphans and vulnerable children (OVC) in the world [10].

In South Africa where the mortality rate of OVC is high, a NEP to assist caregivers/ families to make the right food choices has not been exploited fully. Although there is an existing national policy framework on care and support for OVC in South Africa, there seems to be limited data on nutrition-related information and its application either in counselling or educating the caregivers/families of OVC in the framework [11]. The kind of foods given to OVC depends on the nutrition knowledge of the caregiver/family which can influence the academic achievement of the child.

Academic attainment is described as an outcome of academic performance which is associated with long-term educational feat [12, 13]. It has a vital role in determining health status and life opportunities of OVC by influencing their employment prospects, socio-economic power, QoL and other psychosocial well-being. Children exposed to insufficient or unvaried diets are more likely to encounter academic challenges. Some of the existing literature that examined the relationship between quality of food intake and academic performance reported links between quality of food, poor academic performance, learning capability, physical activities and QoL in both children and adults [12, 14, 15]. These findings suggest that what students eat may affect their academic performance. No review has synthesised the literature investigating the effects of quality of food intakes on the academic performance of OVC in South Africa. Consequently, this study objectives are to (1) document association between OVC’s QoL, individual dietary diversity scores (IDDS), physical activities, body composition and anthropometric status, academic performance and nutrition knowledge, attitude and practices of the caregivers (2) develop NEP based on the outcome of the first objective (3) implement the NEP and examine the impacts on the measurable incomes. The aim of the current study now becomes the development, implementation and impact evaluation of an ENEP for orphans and vulnerable children that will integrate their families/caregivers, schools and communities. It is noteworthy, to know that, the current research protocol premised from the broader study under the incumbent of South African Research Chair in Education and Care in Childhood awarded by the South African National Research Foundation. The incumbent Chair’s research ultimately focuses on developing intervention programmes to reduce the factors of vulnerability and enhance protective factors among OVC with the support of their families/caregivers, schools and communities.

## Methods

### Design

This longitudinal study will be in three phases. The study phases will be conducted consecutively because the phases will be mutually dependent. Phase one will be exploratory descriptive using a mixed method research approach in the qualitative and quantitative research domains. The first phase will provide information that will guide Phase 2 and Phase 3. Phase 2 will be the development of nutrition education materials based on the outcome of phase one. The third phase is an intervention in a quasi-experimental domain.

The overview of the study is illustrated in Figs. 1 and 2.

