### Settings and sampling

The study sites will be in selected schools in Soweto as stated in the broader study of the research chair in the application submitted to the Department of Science and Technology, National Research Foundation and the Faculty of Education Research Ethics Committee of the University of Johannesburg. Convenience sampling will be used to recruit the participants for Phase 1 and 3 of the study. Convenience sampling means to recruit participants who are willing and ready to give their oral and written consents during the data collection.

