### Intervention

The intervention will entail the implementation of the NEP at the orphanage homes. Selected constructs of the SCT and HBM will be incorporated to enhance learning, and positive changes in attitudes and dietary behavior to improve QoL, dietary diversity, physical activities, anthropometric status and academic performance of the OVC. The NEP will address the importance of nutrition in improving QoL and the secondary outcomes, and provide guidance on how to overcome the barriers to healthy eating to enable the caregivers of the intervention group to adopt typical behaviors [49, 51].

The intervention participants will receive nutrition education materials and the 12-week NEP. The NEP is proposed to consist of:(i)a NE trainer’s manual(ii)a participant’s workbook to be used at home by the intervention participants to revise the topics that will be taught. This proposal is expected to enhance participants’ confidence in performing acquired knowledge and skills [49, 51].(iii)flipcharts for pictorial demonstration; so that participants will compile evidence through visual literacy.(iv)a leaflet summarising the NEP for self-learning.

An attendance register will be kept for follow up and measure of attrition rates.

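### Phase 3 is meant to test efficacy, but its groups are formed without random assignment in a convenience sample, so a QoL difference may reflect selection

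*Protocol article*

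**What the plan says.** The Abstract (Background) sets the purpose: to develop and implement the NEP and "to test the efficacy of an evidence-based nutrition education programme (NEP) for OVC". The end of the Background section likewise speaks of evaluating impact. The Sample size section plans two groups, control and intervention.

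On how those groups come about, the article says three things:

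- **Design:** "The third phase is an intervention in a quasi-experimental domain".
- **Settings and sampling:** "Convenience sampling will be used to recruit the participants for Phase 1 and 3 of the study", with the explanation that "Convenience sampling means to recruit participants who are willing and ready to give their oral and written consents during the data collection".
- **Intervention:** "The intervention will entail the implementation of the NEP at the orphanage homes". Under Recruitment and retention of participants, by contrast, children are drawn from secondary schools and followed up either at orphanages or through caregivers.

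No section of the text says how a child, home or school enters the NEP or the control group.

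Data management and analysis gives two safeguards. One is an analysis of variance intended to show that the groups are alike. The other is the use of baseline values as covariates. The covariate sentence refers to the other outcomes; the sentence on QoL, the primary outcome, names no covariate. The Discussion lists only the single province as a limitation.

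**The concern.** An efficacy claim needs groups that differ, apart from the programme, only by chance. Here nothing in the text makes that so. The programme runs in orphanage homes while some children are reached through caregivers, so group could follow where a child lives. It also works through caregivers, so a caregiver's motivation could influence both which group a child is in and how the child's QoL develops.

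If the groups differ in such ways, the QoL comparison at week 12 or week 24 mixes the programme effect with selection. A p-value below 0.05 then no longer carries a 5% false-positive risk. Adjusting for measured baseline values would remove only part of the difference: it does not reach motivation, home resources or a different expected course over time.

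**Working it through.** **Inputs.** From Sample size: difference d = 5 points on a 100-point QoL scale, SD σ = 10, Z for power = 0.84, Z for two-sided 5% = 1.96. From Data management and analysis: testing at the 0.05 level. The size of any selection difference, b, is not in the document. It is an assumption, shown as a range.

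**Step 1: reproduce the plan's figure.** n = 2σ²(0.84 + 1.96)² / d² = 2 × 100 × 7.84 / 25 = 62.72, rounded up to 63 per group. The power at 63 per group is 80.1%. The stated size is right for its inputs, so the issue is bias and not sample size.

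**Step 2: standard error of the group difference.** With children treated as independent and no covariate adjustment, SE = 10 × √(2/63) = 1.782. An observed difference of 1.96 × 1.782 = 3.49 points is already significant.

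**Step 3: chance of a significant result when the programme does nothing.** With a residual selection difference b, this is P(Z > 1.96 − b/SE) + P(Z < −1.96 − b/SE).

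| b (points, assumed) | b/SE | Chance of p < 0.05 at 63 per group |
|---|---|---|
| 0 | 0 | 5% |
| 1 | 0.56 | 9% |
| 2 | 1.12 | 20% |
| 2.5 | 1.40 | 29% |
| 3 | 1.68 | 39% |

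A b of 2.5 is half the difference that the study is sized to detect.

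**Step 4: can the baseline check catch this?** If the baseline SD is also 10, the same formula gives the power of the between-group analysis of variance at baseline. At 63 per group it finds a true 2.5-point imbalance about 29% of the time, so it misses it about 71% of the time. A non-significant result therefore does not show that the groups are similar.

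**The case against.** A quasi-experiment is a legitimate design and this one is openly declared, so preferring randomisation could be called taste. That is fair as far as it goes. What remains is that the aim is worded as efficacy, the design does not support that wording, and confounding is not among the stated limitations.

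The missing rule may stand in Fig. 1 or in a fuller protocol. Matching, or assignment of sites by the investigators, would fit the label. A rule of that kind would help, but under the declared design it would not be expected to be random.

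Three stronger readings are tempting, and the document does not support them:

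- **That volunteers choose their own group, or know it before consenting.** Willingness is given as the condition for entering the study, not for choosing a group. The article is silent on blinding and on the order of consent and assignment.
- **That a ready list of consented sites already exists from Phase 1, so that a random draw would be free.** Phase 1 is planned large ("QoL, dietary intakes, body composition, and anthropometric status, physical activities, and AP of 520 OVC in Soweto will be assessed using standard techniques"), but site-level consent is described only for schools. No list or count of orphanage homes is given, and assigning whole sites has a clustering cost.
- **That the larger enrolment makes matters worse.** At 126 analysed per group the rates for b = 1, 2, 2.5 and 3 would be 13%, 36%, 51% and 66%. But the doubling from 63 to 126 is there to cover non-response and dropout, so 63 is the planned analysed size.

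The size of b has no anchor in the document. Moreover, the SD and the difference are described as being between pre and post intervention. If they refer to change scores, a stable difference between groups cancels and b must be a difference in trajectory, which is a stronger assumption. This limits the figures to an illustration; it does not remove the problem.

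**Conclusion.** The point holds in this form: an efficacy aim is paired with a declared quasi-experiment in convenience-recruited participants, with no random assignment in the text and safeguards that cannot remove unmeasured selection. Followed as written, the plan can lead to a wrong efficacy conclusion on QoL.

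The illustrated size is a false-positive risk of 9% to 39%, against a nominal 5%. It rests on a selection difference of 1 to 3 points (assumed), SD 10, independent children, no covariate adjustment, no true effect and 63 analysed per group. A reader might infer that selection will produce the result, or that the bias is known to be this large. Neither is shown: the document establishes that selection is possible and uncontrolled, not that it occurs.

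**What to change.** **Main change, in Design and Settings and sampling.**

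1. Complete consent and baseline measurement for Phase 3 first.
2. Then assign the units through which the NEP is delivered to NEP or control by a computer-generated draw. These units are orphanage homes, or caregiver or school groups where children do not live in homes.
3. Pair or stratify the units on baseline mean QoL and size.
4. Allow for clustering by that unit in the analysis, and qualify the power stated under Sample size accordingly.

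**Where random assignment is not possible.** State the assignment rule. In the Abstract, replace the aim of testing efficacy with estimating an adjusted association. Adjust QoL for baseline QoL. Add selection and confounding to the limitations in the Discussion.

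**Cost.** The phases run consecutively, so there is time for the draw before delivery starts. Homes would have to be listed, some sites may refuse assignment to control, and with few sites chance imbalance remains. Precision falls below what Sample size states if outcomes cluster. For example, with an assumed intracluster correlation of 0.05 and 20 children per site (neither is in the document), the design effect is 1 + 19 × 0.05 = 1.95, and 63 × 1.95 = 122.85, or about 123 analysed per group. Clustering also affects the present design, so this loss is no reason to keep it. The fallback costs only wording and one covariate.

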**Fig. 1 Fig1:**
[figure not shown]
Overview of the study protocol

**Fig. 2 Fig2:**
[figure not shown]
Conceptual frameworks for developing and implementing a nutrition education programe for OVC

### Settings and sampling

The study sites will be in selected schools in Soweto as stated in the broader study of the research chair in the application submitted to the Department of Science and Technology, National Research Foundation and the Faculty of Education Research Ethics Committee of the University of Johannesburg. Convenience sampling will be used to recruit the participants for Phase 1 and 3 of the study. Convenience sampling means to recruit participants who are willing and ready to give their oral and written consents during the data collection.

### Sample size

The sample size in this study was estimated based on the expected number of consenting participants in the two groups (control and the intervention group). This study desired 80% power (Z_β_ = 0.84) to estimate sample size with confidence interval (Z_∝/2_ = 1.96) of 95% as used in previous studies [16]. The investigator desires to detect a difference (d) of 5 points on a 100 point scale of QoL constructs between pre and post intervention [16, 17]. Standard deviation (*σ*) of 10 is expected in the QoL constructs between pre and post intervention [17]. Sample size (n) of 63 OVC per group (control and the intervention) to make a total of 126 OVC using the formular below is projected [18, 19].

*n* = 2(*σ*)2(*Z*_*β*_ + *Z∝*/2)2 ÷ *d*2

In order to compensate for non-response and drop out, 100% will be added to make a sample size of 126 anticipated consenting participants per group to make a total of 252 participants [18]. For the need’s assessment (Phase 1) a total of 252 is appropriate but 520 is proposed in order to further compensate for non-response and drop out.

### Recruitment and retention of participants

Recruitment of participants will start during the start of the second term. We estimated that a total of 520 students aged (12–17 years) will be selected. Participants will be chosen from secondary schools in Soweto. The OVC will be followed up at their various orphanages or through their caregivers.

### Eligibility criteria

Informed consent of school teachers will be obtained for school participation and if a school declines, a nearby alternative school will be approached. Students in the participating schools will be invited for briefing if they meet the following criteria:Are within the age range of 12–17 yearsLost one or both parentsGive both oral and written consents

### Measures

All the measures are composed of items adapted from published studies. The QoL questionnaire that will be used in this study has previously been validated with acceptable psychometrics values.

### Primary outcome

QoL will be measured using Kidscreen health-related QoL questionnaire for children and adolescents. This questionnaire has previously been validated in South Africa and shows acceptable psychometrics reliability of 0.76–0.81 [20].

### Secondary outcomes

The following data will be collected to assess secondary outcomes.

#### (*a) Dietary intake assessments*

***Food intakes using photovoice***

The method of data collection here will be emancipatory participatory approach using photovoice and photo-assisted focus group discussions. Photovoice is a qualitative research method that enables participants to be involved in data collection by representing their experience, perception, concepts, and voices using photographs [21, 22]. The photographs will be used to capture participants’ viewpoints in the form of storytelling. It will enable participants of thisresearch to contextualise the photographs and have shared multiple viewpoints by explaining what the photographs mean to them during assisted group discussions [22–24]. A disposable camera with limited number of films will be provided to the caregivers/families of the OVC to take pictures of foods and environment where foods are provided to the OVC [25]. Participants will be trained in the use of the disposable camera. The caregivers/families OVC will be required to take pictures of food intakes OVC for three days, one of which must be weekend (Training will be provided). Such caregivers/families of OVC will be engaged in photo-assisted focus group discussions that is, they will be expected to explain what the pictures mean to them.

It will be clearly stated to the participants that, there will be no pictures of people but pictures of foods and environment only. The pictures will be used to initiate dialogue on the food intakes and food security of the OVC. The cameras will be recycled immediately the appropriate pictures have been selected. The length of the interview is estimated to be 35 min with another 25 min for discussion on the pictures taken. The group discussions will engage participants in reflective perspective analysis on the healthiness of the foods in which the photograph is taken during the three-day period.

The needs that will be identified in the food intakes of the OVC will be incorporated into the NEP that will be developed and implemented to capacitate the caregivers/families of OVC.

The photovoice will be followed with photo-assisted focus group discussions.

Photovoice is well documented in disciplines such as anthropology, health, and sociology [26, 27]. The process has been reported to be effective in arriving at more valid and reliable evidence-based data collection [26]. Experience from verbal expression may be challenging to measure quantitatively, that does not mean that quantitative data are not reliable [28]. Therefore, photovoice will be combined with a single day 24 h recall to add richness and comprehensiveness to the method of data collection [29].
